### Adverse events

2.6

Adverse events (AEs) refer to patient injuries caused by medical care (19). Serious adverse events (SAEs) refer to medically related events that result in death, are life-threatening, require hospital admission or prolong hospital stay, or cause persistent or significant disability. Although adverse effects of CNSI and ICG have not been observed in preclinical studies, any forms of adverse events should be systematically recorded.

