### Interventions

2.4

In the CNSI group, the patients are given injections of CNSI (50 mg/dose) produced by Chongqing Lummy Pharmaceutical Co., Ltd. in the endoscopy division 1 day before surgery. CNSI is injected submucosally at 4 points (proximal side, distal side, and left and right sides) 0.5-1 cm from the tumor edge under endoscopy. The optimized dose for each point is approximately 0.25 ml (**Figure 2A**).

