### Outcomes

2.5

The primary outcome of this study is to determine the number of LNs retrieved. The secondary outcomes are to determine the LN staining (or fluorescence) rate (Number of staining or fluorescence LNs/Total number of retrieved LNs), LN staining (or fluorescence) rate at each station, stained (or fluorescent) LN positive rate(Number of staining or fluorescence positive LNs/Total number of positive LNs), stained (or fluorescent) LN negative rate(Number of staining or fluorescence negative LNs/Total number of negative LNs), nonstained (or nonfluorescent) LN positive rate(Number of nonstaining or nonfluorescence positive LNs/Total number of positive LNs), nonstained (or nonfluorescent) LN negative rate(Number of nonstaining or nonfluorescence negative LNs/Total number of negative LNs), LN metastasis rate(Number of metastasis LNs/Total number of retrieved LNs), number of metastatic LNs, complication and mortality rates within 30 days, 3-year disease-free survival (DFS), 3-year overall survival (OS), recurrence pattern within 3 years, intraoperative blood loss volume, time spent retrieving LNs, and postoperative recovery (exhaust time after surgery, feeding time after surgery, duration of postoperative hospital stay).

Any complications should be recorded and reported. There are mainly two complications related to the procedure: intraoperative complications and postoperative complications. The former includes bleeding, injuring the viscera, lymphatic leakage and so on. The latter should be classified according to the Clavien−Dindo classification system.

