## Discussion

3

Despite the serious burden of GC in China, the public awareness of risk factors or warning symptoms and screening is low, and there is a lack of screening programs (20). Therefore, the majority of GC are detected at an advanced stage, and at this moment, LN metastasis usually occurs. It is well known that LN metastasis is one of the most important prognostic factors for GC patients, and D2 LN dissection has gradually become the mainstream treatment to improve patient outcome (21). The mean number of LNs dissected in Western European countries was 29.5, which is slightly higher than that in China (22). This condition might be associated with the insufficient LN dissection intraoperatively and the false idea that postoperative LN dissection should be completed by a pathologist. Currently, an increasing number of studies have begun to focus on LN tracers, and an increasing number of gastrointestinal surgeons have started using carbon nanoparticle suspension injection or indocyanine green.

A number of interesting differences were identified through our analyses of CNSI and ICG. First, taking an appropriate amount of time to dissect LNs as an example, the LNs are stained black using CNSI, while the LNs labeled with ICG have the ability to generate strong fluorescence emission in certain cases. When utilizing CNSI as a tracer of LNs, surgeons can dissect the LNs under direct vision without the assistance of other instruments. However, if surgeons intend to use indocyanine fluorescence imaging to guide the postoperative nodal dissection, the fluorescence imaging mode must be available, and the wear and tear of the instrument and the burden on surgeons and operating room nurses will increase, which may prolong the time needed for dissecting the LNs. Second, compared with CNSI, ICG may have the potential to decrease the risk of anastomotic fistula with the assistance of examining the blood supply of the anastomosis. Third, CNSI extravasation into gastric serosa will contaminate the surgical fields and increase the difficulty of surgically dissecting the gastric tumor, but surgeons can switch between the fluorescence mode and normal mode to avoid the adverse effects caused by ICG extravasation (15).

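### The AE and SAE definitions in Section 2.6 build a causal judgement into what gets recorded, in an open-label trial that sets out to compare safety

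*Protocol article*

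**What the plan says.** Section 2.6 (Adverse events) contains three statements that bear on each other:

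- The AE definition: "Adverse events (AEs) refer to patient injuries caused by medical care (19").
- The SAE definition, which opens "Serious adverse events (SAEs) refer to medically related events that result in death, are life-threatening" and goes on to the usual seriousness criteria.
- The recording instruction, in a sentence that names both tracers: "any forms of adverse events should be systematically recorded".

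Section 2.5 (Outcomes) deals with complications separately. It lists "complication and mortality rates within 30 days" as a secondary outcome, instructs that "Any complications should be recorded and reported", and then says: "There are mainly two complications related to the procedure: intraoperative complications and postoperative complications". It does not say when the 30 days begin. Section 2.4 (Interventions) places the tracer injection in both arms "in the endoscopy division 1 day before surgery".

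Section 2.3 says that surgeons and participants cannot be blinded and that allocation is not concealed; only the pathologists are blinded. Section 2.8 has surgeons collecting the data and gives a comparison of safety as part of the study's purpose.

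**The concern.** In a comparative trial the usual protection is to record every untoward event first and to judge its relation to treatment afterwards, as a separate item. A definition that requires causation reverses that order: the judgement becomes a condition of entry into the data. Two things follow. Events considered unrelated leave no trace, so nobody can later check whether they were divided evenly between the arms. And the decision to leave them out rests with staff who know which tracer was given. Safety is one of the two things this trial sets out to compare, so the rule for collecting safety events has to be sound. A statistical analysis plan cannot repair it, because it can only work on what was recorded.

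**Working it through.** The plan states no figure on this point, so the check sets the passages side by side.

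**Step 1. What the AE definition requires.** Section 2.6 asks for two things: an injury to the patient, and causation by medical care. An event that meets the first but is judged not to meet the second is not an AE.

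**Step 2. What the SAE definition requires.** It asks for a seriousness criterion and for the event to be medically related. That phrase is looser than the AE wording. Placed directly after a causal AE definition, it is most naturally read as a second causal condition. If it was meant only as medical in nature, the text should say so.

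**Step 3. Whether the recording instruction removes the condition.** There are two readings.
- If the term keeps the meaning given at the start of the section, the instruction covers all forms of care-caused injury, and the filter stays.
- If the term has its ordinary wide meaning, the instruction contradicts the definition, and staff have two different rules.

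Neither reading yields a clear rule to record events whatever their cause.

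**Step 4. Who applies the condition.** By Sections 2.3 and 2.8, data collection is by surgeons in a trial where surgeons cannot be blinded. Nothing in the article gives the blinded pathologists a role in judging safety events.

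**Step 5. Which events are affected.**

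| Event | Covered as written? |
|---|---|
| Reaction on the day before surgery, recognised as due to the injection | Yes. The injection is medical care, so the AE definition is met |
| Intraoperative or postoperative complication | Yes, under Section 2.5, which has no causal test of the Section 2.6 kind |
| Death within 30 days | Yes, under the mortality outcome in Section 2.5 |
| Non-fatal event judged unrelated to care and not regarded as a complication | No |

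The loss is confined to the last row.

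**Step 6. The 30-day window.** Exposure to the tracer begins one day before surgery. The 30-day outcome has no stated start, so it could run from either day. The two readings differ by one day.

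**The case against.** The strongest reply is that the filter concerns medical care in general, not the tracer. Patients in both arms have an endoscopic injection and a laparoscopic exploration, and those who proceed have a D2 gastrectomy. Most perioperative events would be put down to care in either arm, and the definition never asks staff to blame a particular tracer. A preference for one tracer therefore has no obvious route to a different attribution rate by arm. That stands as a limit on size: the documents do not show that the filter would favour either group. It does not make the definition right, because unattributed events would still go unrecorded and their balance could not be checked.

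A reader might infer more than the text supports, in three ways.

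- *That tracer reactions before surgery are lost.* They are not. An injury from the injection is caused by medical care, and the recording instruction is given with both tracers in view.
- *That complications count only if intraoperative or postoperative.* Section 2.5 says these are the main kinds, not the only ones, and requires any complication to be recorded.
- *That patients injected but stopped at laparoscopy drop out of safety recording.* Section 2.4 makes gastrectomy conditional on the exploration and cytology findings, but nowhere ends safety recording for those patients.

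It is also fair to say that the safety analysis set, the layout of the case report form and the AE tables belong to the full protocol or analysis plan, which are not shown. Their absence from the article is no fault. The definition is different, because the article states it.

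**Conclusion.** Wrong as written, with a narrow reach. The AE and SAE definitions in Section 2.6 make a causal judgement by unblinded staff a condition of recording, and they sit uneasily with the instruction beside them. Events judged unrelated to care, and not picked up as complications or deaths, fall outside AE and SAE recording and cannot be recovered later.

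No numerical size can be given. The article states neither an expected AE rate nor how often events would be judged unrelated, and any assumed difference in attribution between the arms would have no support in it. The conclusion assumes that the definitions are applied as printed and that the full protocol does not replace them. The unstated start of the 30-day window is a minor matter of clarity.

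**What to change.** In Section 2.6:

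- Define an AE as any untoward medical occurrence from tracer injection onward, whatever its cause.
- Define an SAE as an AE that meets one of the seriousness criteria already listed, and remove the medically related qualifier.
- Record relatedness as a separate judgement, made after the event has been entered.

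In Section 2.5, as a minor clarification, state whether the 30 days for complications and mortality run from injection or from surgery.

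The change takes a few sentences. Its cost is slightly higher recorded AE counts and the work of recording relatedness separately. The primary outcome and the sample size are not affected. If recruitment or follow-up has already run under the printed definition, the report should say so and describe the AE data as limited to events attributed to care.

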### Sample size

2.7

The sample size for this study was calculated based on previous research by our team and computed by PASS version 11. Eligible subjects were randomly assigned (1:1) into the CNSI group and the ICG group. All analyses were two-sided with α=0.05 and β=0.80. the prospective mean number of the LNs retrieved in the CNSI group was 56.93. The prospective mean number of the LNs retrieved in the ICG group was 50.52. The total sample size was 96 (48 per group) after taking into account a 10% dropout rate in each group. The planned recruitment period is 1 year, and the follow-up duration is 3 years.

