### Study design

2.1

The current study is a prospective, randomized, open label, single-center, noninferiority clinical trial. The study takes place in the Fourth Hospital of Hebei Medical University. Patient enrollment started on 20 January 2021, and the trial is expected to end on January 20 2025. **Figure 1** summarizes the design of the trial, and each of the trial aspects is described in detail below.

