### Data collection and analysis

2.8

Designated and trained surgeons collect the data from the pathology reports and operative reports. The focus of the data should contain clear information about the tumor location, tumor size, histopathologic type, tumor differentiation degree, Lauren classification, vascular tumor embolus, nerve invasion, immunohistochemistry results and pathological findings of the LNs at each station. Long-term prognosis data are collected *via* follow-up up until 3 years after the surgical operations. The follow-up should consist of a 3-month interval from 0–2 years and a 6-month interval in the third year. The main follow-up items included routine physical examination, tumor marker detection (CEA, CA199, CA724 and AFP), abdominal CT, and annual electronic gastroscopy. The follow-up included an outpatient follow-up, a telephone follow-up and a short message platform follow-up. Further evaluation and treatment should be performed if relapse occurs.

The purpose of this study is to compare the safety and efficacy of CNSI and ICG during radical gastrectomy. The primary objective is to determine the number of LNs retrieved. Comparability analysis will be performed on the baseline data to determine whether the two groups are comparable. The number of patients, mean, standard deviation, median, maximum, and minimum will be listed. Descriptive data will be presented as the mean ± SD, while categorical data will be presented as the number and percentage (%). The independent samples t test or nonparametric test will be used to analyze continuous data, and the chi-square test or Fisher’s exact test will be used to analyze categorical variables. It is valuable to analyze the influence of CNSI (ICG) staining or other factors on the number of LNs detected according to the statistical analysis. We can also research the effect of CNSI (ICG) staining on the operative time, intraoperative bleeding volume, intraoperative transfusion volume and postoperative complications. Survival analysis will be performed using the Kaplan−Meier method, and the log rank test will be used to test the difference in survival rates between the two groups. SPSS 26.0 statistical software will be used for statistical analysis. P<0.05 will be considered to indicate statistically significant differences.

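### The sample size section prints β = 0.80, which literally means 20% power; power of 0.80 was most likely mislabelled, and the SD needed to reproduce 48 per arm is not quoted.

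*Protocol article*

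**What the plan says.** Section 2.7 (Sample size) of the protocol article gives the error rates as "All analyses were two-sided with α=0.05 and β=0.80". The expected means are 56.93 nodes with carbon nanoparticles ("the prospective mean number of the LNs retrieved in the CNSI group was 56.93") and 50.52 with indocyanine green ("The prospective mean number of the LNs retrieved in the ICG group was 50.52"). Allocation is 1:1, and the result is "The total sample size was 96 (48 per group) after taking into account a 10% dropout rate in each group". The source is described only in general terms: "The sample size for this study was calculated based on previous research by our team and computed by PASS version 11".

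The article states neither a power nor an SD for the number of nodes. Section 2.8 (Data collection and analysis) says that SDs will be reported with the results, and gives the test as "The independent samples t test or nonparametric test will be used to analyze continuous data". Section 2.1 (Study design) describes the trial differently from a two-sided comparison: "The current study is a prospective, randomized, open label, single-center, noninferiority clinical trial".

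**The concern.** By the usual definition β is the probability of missing a true difference of the assumed size, and power is 1 − β. Printed as it is, β = 0.80 says that the trial would miss a true difference of 6.41 nodes four times in five. This is a wrong statement in the text, not a detail left for another document.

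It concerns the calculation that justifies the 96 patients for the primary outcome. A reader would normally settle a slip of this kind by putting the printed inputs into the formula and seeing which power returns the printed sample size. Here that is not possible, because the SD is not quoted. At stake is the accuracy of the stated design power and whether a reader can check it. The conduct of the trial is not affected.

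**Working it through.** **Inputs from section 2.7.** Two-sided α = 0.05; means 56.93 and 50.52; allocation 1:1; dropout 10% per group; 48 per group, 96 in total. The SD is not given.

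**Step 1: literal meaning.** Power = 1 − β = 1 − 0.80 = 0.20.

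**Step 2: difference.** 56.93 − 50.52 = 6.41 nodes.

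**Step 3: evaluable patients per arm.** 43 / 0.9 = 47.8, rounded up to 48. Inflating the other way, 43 × 1.1 = 47.3, also gives 48. By either method 42 gives 47 and 44 gives 49, so 43 is the only base that leads to 48.

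**Step 4: can the 96 be reproduced?** Not forwards, because the formula needs the SD:

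n per arm = 2 × (z for α + z for power)² × SD² / difference²

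It can only be solved backwards for the SD.

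**Step 5: SD implied by 80% power.** This assumes a two-sided superiority comparison of means.

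- Normal approximation: SD = 6.41 × √(43/2) / (1.960 + 0.842) = 29.72 / 2.802 = 10.6.
- Noncentral t: SD = 10.49.
- Forward check with SD 10.5 (normal approximation): 2 × 2.802² × 10.5² / 6.41² = 42.1, rounded up to 43 per arm, then 48 after dropout and 96 in total.

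An SD of 10.5 is 10.5 / 50.52 = 21% of one assumed mean and 10.5 / 56.93 = 18% of the other.

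**Step 6: power if the SD was larger.** Noncentral t, 43 per arm, difference 6.41, two-sided 5%. All SDs are assumed.

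| Assumed SD | Power |
|---|---|
| 10 | 84% |
| 10.5 | 80% |
| 12 | 69% |
| 15 | 50% |
| 18 | 37% |
| 20 | 31% |

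**Step 7: dependence on the test.** If the software was run for noninferiority, the implied SD is different. No margin is printed, so the margins here are assumed. With 43 per arm, one-sided 2.5%, 80% power and a true advantage of 6.41, margins of 2, 3 and 5 nodes give SDs of about 13.8, 15.4 and 18.7. The 10.5 in Step 5 therefore holds only for the two-sided superiority test.

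**The case against.** The strongest reply is that this is a slip of notation. Writing 0.80 beside β instead of beside power changes neither the number of patients, the analysis nor the conduct, and the abstract reports the 96 as already enrolled. That stands, and it sets the scale of the point. It does not make the printed statement correct, and no other sentence in the article overrides it.

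A second reply is that a journal article condenses a fuller protocol, so an SD missing here may well be recorded there. That also stands: the missing SD is not an error by itself. It is worth requesting because it is the input that would confirm what the β figure was meant to be.

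Three stronger readings are tempting, and the document supports none of them.

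- A reader might infer that the trial could equally have been planned at 20% power. Back-solving at 20% power does return an SD, about 26.4 by the noncentral t. That is weak evidence, because with the SD unprinted any power fits some SD. A value of 0.80 is far more plausible as a power than as a type II error.
- A reader might infer that a nonsignificant primary result could not be interpreted. It could: the estimated difference and its confidence interval, using the SD observed in the trial, carry that interpretation. The symbol printed in section 2.7 does not affect them.
- A reader might treat 10.5 as a fixed limit for the SD. It depends on the test assumed, as Step 7 shows.

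**Conclusion.** The error is real but limited. As written, section 2.7 states a type II error of 80%, that is 20% power, for the primary outcome. Most likely a power of 0.80 was mislabelled.

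Whether 48 per arm delivers 80% cannot be verified from the article. Under a two-sided superiority t test with a difference of 6.41 and 43 evaluable per arm, it does so only for an SD of about 10.5 or less; power would be about 69% at SD 12 and 50% at SD 15. The true SD is unknown here, so these figures show how sensitive the power is and are not an estimate of what the trial has. They rest on reading the calculation as superiority, which section 2.7 suggests through its two-sided α and two expected means, but which does not match the noninferiority label in section 2.1.

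**What to change.** 1. Retrieve the PASS output and confirm which power was entered. If it was 80%, replace the β statement in section 2.7 with *power 80% (β = 0.20)*.
2. Quote the SD used and its source in the team's previous research, and show that it leads to 43 evaluable and 48 enrolled per arm.
3. Name the test that the calculation was run for. If it was a noninferiority calculation, give the margin and the one-sided α, since the SD consistent with 48 per arm then differs from 10.5.
4. If the SD used was larger than the confirmed test allows for 80% power, keep n = 96 and restate the power which that SD gives.

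The cost is a change of wording and, at most, one re-run of the calculation. The restated power may be less favourable. No extra patients and no change to the analysis are needed.

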### Data collection and analysis

2.8

Designated and trained surgeons collect the data from the pathology reports and operative reports. The focus of the data should contain clear information about the tumor location, tumor size, histopathologic type, tumor differentiation degree, Lauren classification, vascular tumor embolus, nerve invasion, immunohistochemistry results and pathological findings of the LNs at each station. Long-term prognosis data are collected *via* follow-up up until 3 years after the surgical operations. The follow-up should consist of a 3-month interval from 0–2 years and a 6-month interval in the third year. The main follow-up items included routine physical examination, tumor marker detection (CEA, CA199, CA724 and AFP), abdominal CT, and annual electronic gastroscopy. The follow-up included an outpatient follow-up, a telephone follow-up and a short message platform follow-up. Further evaluation and treatment should be performed if relapse occurs.

The purpose of this study is to compare the safety and efficacy of CNSI and ICG during radical gastrectomy. The primary objective is to determine the number of LNs retrieved. Comparability analysis will be performed on the baseline data to determine whether the two groups are comparable. The number of patients, mean, standard deviation, median, maximum, and minimum will be listed. Descriptive data will be presented as the mean ± SD, while categorical data will be presented as the number and percentage (%). The independent samples t test or nonparametric test will be used to analyze continuous data, and the chi-square test or Fisher’s exact test will be used to analyze categorical variables. It is valuable to analyze the influence of CNSI (ICG) staining or other factors on the number of LNs detected according to the statistical analysis. We can also research the effect of CNSI (ICG) staining on the operative time, intraoperative bleeding volume, intraoperative transfusion volume and postoperative complications. Survival analysis will be performed using the Kaplan−Meier method, and the log rank test will be used to test the difference in survival rates between the two groups. SPSS 26.0 statistical software will be used for statistical analysis. P<0.05 will be considered to indicate statistically significant differences.

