### Eligibility criteria

2.2

The inclusion criteria are as follows: (1) aged 18–75; (2) histologically proven gastric adenocarcinoma on biopsy (papillary adenocarcinoma, tubular adenocarcinoma, mucous adenocarcinoma, signet-ring cell carcinoma or poorly differentiated adenocarcinoma); (3) proven clinical stage of cT1-4a N0/+ M0 by ultrasound endoscopy, enhanced CT/MRI examination or diagnostic laparoscopy according to the TNM classification of the American Joint Committee on Cancer (AJCC cancer staging manual, eighth edition); (4) without distant metastasis and no invasion of adjacent organs; (5) a preoperative Eastern Cooperative Oncology Group (ECOG) score of 0 or 1; (6) a preoperative American Society of Anesthesiologists (ASA) score of I-III; and (7) signed a written informed consent form.

The exclusion criteria are as follows: (1) pregnant or lactating women; (2) patients with severe mental disorder; (3) a history of upper abdominal surgery (with exception of laparoscopic cholecystectomy); (4) a history of gastrectomies, endoscopic mucosal resection (EMR) or endoscopic submucosal dissection (ESD); (5) enlarged or bulky regional LNs according to preoperative imaging and larger than 3 cm at the long diameter; (6) the tumor invades the duodenum or esophagus; (7) Borrmann type IV GC; (8) history of other malignant tumors within the last 5 years; (9) received previous neoadjuvant radiotherapy or chemotherapy; (10) history of myocardial infarction or unstable angina within the last 6 months; (11) history of cerebrovascular accident within the last 6 months; (12) undergoing sustained systemic corticosteroid treatment within 1 month prior to surgery; (13) emergency surgery due to GC complications (bleeding, perforation, or obstruction); and (14) FEV1 <50% predicted value.

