**Figure 2 f2:**
[figure not shown]
Endoscopic injection of lymph node tracer. **(A)** Carbon nanoparticle suspension injection; **(B)** Indocyanine green.

For those who were randomly assigned to the ICG group, ICG (25 mg/dose) produced by Dandong Yichuang Pharmaceutical is marked in the endoscopy division 1 day before surgery and is injected submucosally at 4 points (proximal side, distal side, and left and right sides) 0.5-1 cm from the tumor edge under endoscopy. The optimized dose for each point is approximately 0.5 ml (**Figure 2B**).Both procedures are performed by a designated, experienced endoscopic specialist.

Laparoscopic exploration and detection of free peritoneal cancer cells are necessary in the first step of the surgical procedure to exclude adjacent organ infiltration and peritoneal metastasis. When the patient is positioned in the reverse Trendelenburg position (described as the foot-down and head-up supine position), 800 ml of normal saline is routinely used to wash the area near the carcinomatous foci of GC and is then re-collected as much as possible. It is important to collect at least 300 ml of the flushing fluid from the pelvic cavity. Cytology examination is then immediately performed on the flushing fluid collected. If the peritoneum is free of metastasis and peritoneal lavage cytology is negative, standard laparoscopic or robotic radical gastrectomy with D2 lymphadenectomy is then performed by the designated and experienced team of surgeons according to the Japanese Gastric Cancer Treatment Guidelines 2014. Distal gastrectomy for LN dissection included LN station 1, 3, 4 sb, 4d, 5, 6, 7, 8a, 9, 11p, 12a.

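### The primary node count is left to an unadjusted t test or a nonparametric test with no rule for choosing; one prespecified covariate-adjusted mean difference would close the choice and modestly improve precision

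*Protocol article*

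**What the plan says.** Section 2.5 of the protocol article sets the endpoint: "The primary outcome of this study is to determine the number of LNs retrieved". Section 2.8 gives one sentence on how such data are tested: "The independent samples t test or nonparametric test will be used to analyze continuous data". It names no criterion for preferring one test and no covariates. The same section plans a check of baseline comparability, and remarks that it would be worthwhile to study how staining or other factors influence the node count, but it attaches no model to that remark.

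Section 2.7 bases the sample size on means: "the prospective mean number of the LNs retrieved in the CNSI group was 56.93" and "The prospective mean number of the LNs retrieved in the ICG group was 50.52".

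Four other places bear on the point:
- Section 2.2 admits patients with "proven clinical stage of cT1-4a N0/+ M0". It excludes tumours invading the duodenum or esophagus and Borrmann type IV disease, but does not otherwise limit the part of the stomach involved.
- Section 2.4 lists stations for one operation only: "Distal gastrectomy for LN dissection included LN station 1, 3, 4 sb, 4d, 5, 6, 7, 8a, 9, 11p, 12a".
- Section 2.3 describes 1:1 allocation from a random number table, unconcealed, with no stratification mentioned.
- Section 2.8 says the collected data should include "clear information about the tumor location, tumor size, histopathologic type", taken from surgical and pathology records.

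**The concern.** Two things are at stake.

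**Choice of test.** A t test addresses a difference in means; a rank test addresses a shift between distributions. They can disagree, and only the first matches the quantity used to size the trial. The trial is open label, and surgeons both retrieve the nodes and collect the data. A choice of primary test that is still open when results are visible is avoidable flexibility.

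**Precision and balance.** The endpoint is a total over all stations removed. A station list specific to distal gastrectomy suggests that the stations removed depend on the resection, and hence on where the tumour lies. If so, location and stage contribute between-patient variance that an unadjusted test leaves in the error term. A chance imbalance between arms would also shift the observed difference. With about 43 evaluable patients per arm and no described stratification, such imbalances are not rare. The plan checks baseline comparability but does not say what follows if the arms differ.

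**Working it through.** **Inputs from the documents.** Difference = 56.93 − 50.52 = 6.41 nodes. Section 2.7 states "All analyses were two-sided with α=0.05 and β=0.80"; I read this as two-sided 5% and 80% power. There are 48 per group after 10% dropout, so 48 × 0.90 = 43.2, about 43 evaluable per arm. The SD is not stated. The trial is labelled noninferiority without a margin, so I treat the calculation as a test of a difference, which is what the stated inputs support.

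**Reproducing the plan's figure.** The stated 96 cannot be derived directly without an SD, but it can be back-solved:
- SD = 6.41 / (1.960 + 0.842) × √(43/2) = 10.6.
- Forward, with SD 10.5: n = 2 × 2.802² × 10.5² / 6.41² = 42.1, so 43 per arm; 43/0.90 = 47.8, so 48 per arm and 96 in total.
- SD 10 gives 44 per arm and SD 11 gives 53, so about 10.5 is the value consistent with the stated number.

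**Power of the unadjusted test.** SE = 10.5 × √(2/43) = 2.264; noncentrality = 6.41/2.264 = 2.83; 84 degrees of freedom; power 79.9%. The plan meets its own target without adjustment.

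**Power with adjustment.** Let the covariates explain a share R² of the variance (an assumption; the documents give no figure) and use k degrees of freedom, with N = 86. Then

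SE = 10.5 × √(1 − R²) × √(2/43) × √[(N − 3)/(N − 3 − k)], tested on N − 2 − k degrees of freedom.

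The last factor is the expected cost of estimating the covariate effects: 83/80 = 1.038 in variance for k = 3, and 83/77 = 1.078 for k = 6. For example, with R² = 0.20 and k = 3, SE = 2.063, noncentrality = 3.107 and power = 86.7%.

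| R² (assumed) | no charge for k | k = 2 | k = 3 | k = 6 |
|---|---|---|---|---|
| 0.05 | 81.9% | 80.9% | 80.4% | 78.9% |
| 0.10 | 83.9% | 83.0% | 82.5% | 81.0% |
| 0.20 | 87.9% | 87.1% | 86.7% | 85.3% |
| 0.30 | 91.7% | 91.0% | 90.7% | 89.6% |

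Three degrees of freedom correspond to location, T and N each in two groups; six correspond to three locations, four T categories and N0 against N+. Simulating 20,000 trials per setting for k = 2, 3 and 6 agrees to within one percentage point.

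**If the SD is larger.** At SD 16 (an assumption with no source in the documents), unadjusted power is 45%. Adjusted power at R² 0.10, 0.20 and 0.30 is 48%, 52% and 58% with k = 3, and 46%, 51% and 56% with k = 6.

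**Chance imbalance.** Assume a tumour location with 40% prevalence and simple randomization. The probability that the arms differ by at least 15 percentage points is about 12% with 48 per arm and 15% with 43. If the resections concerned differed by 5 to 10 nodes (assumed), a 15-point gap would move the arm difference by 0.15 × 5 = 0.75 to 0.15 × 10 = 1.5 nodes, which is 12% to 23% of 6.41.

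**The case against.** The strongest reply is that nothing here is wrong. An unadjusted comparison of randomized arms is valid, and its power matches the stated target at the implied SD. That stands. A reader might infer that the trial is underpowered or its comparison biased because covariates are ignored; the documents do not support either.

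Second, covariate choice and test selection are often settled in an analysis plan, which is not shown, and section 2.8 leaves room to study other factors. This lowers the weight of the point but does not remove it. The article does state a method for continuous outcomes, that method offers two tests, and a later plan would have to resolve it.

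Third, no document gives node yield by location, resection or stage. The link from location to count can be inferred from the distal-only station list but is not shown, so the R² values remain assumptions. This stands too.

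Fourth, shrinking the SD without charging for the covariates gives 84%, 88% and 92%. Those figures are too favourable for a model with several categories: with six degrees of freedom the gain at R² = 0.10 is about one point, and at R² = 0.05 power falls slightly.

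Finally, one might hope that adjustment would answer the lack of allocation concealment. It would not: steering on unmeasured features is untouched by adjusting for location and stage.

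**Conclusion.** The point holds as a worthwhile improvement. The plan leaves the primary test open between two methods that target different quantities, while sizing the trial on only one of them. It also forgoes precision from baseline factors that could be recorded before randomization.

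The gain is modest. From about 80%, power rises to roughly 83%, 87% or 91% with two or three covariate degrees of freedom, or 81%, 85% or 90% with six, for assumed R² of 0.10, 0.20 and 0.30. There is little or no gain at 0.05. These figures rest on a back-solved SD of 10.5, 43 evaluable patients per arm and assumed R². The open choice of test is the firmer half, because it needs none of these assumptions.

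**What to change.** Before any comparison by arm, name one primary analysis:
- A linear model of total node count on arm, with a small set of baseline covariates: tumour location from pre-randomization endoscopy or CT, and clinical T and N in few categories.
- Report the adjusted mean difference with its 95% CI, so that the estimand matches the sample-size calculation.
- Keep the unadjusted t test and the rank test as sensitivity analyses.
- Do not adjust for anything the tracer can affect, such as staining, retrieval time or the stations actually yielding nodes.

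No extra patients are needed, and the model costs only a few degrees of freedom. It is not purely a change of wording: section 2.8 takes location from surgical and pathology records, so it must be extracted from preoperative records. Timing also matters. The abstract reports 96 patients enrolled, and node counts are known soon after surgery. If arms have already been compared, the adjusted model should be reported as a labelled later addition. The lack of allocation concealment needs its own answer.
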